## Abstract

**Background:**

Modern methods in intensive care medicine often enable the survival of older critically ill patients. The short-term outcomes for patients treated in intensive care units (ICUs), such as survival to hospital discharge, are well documented. However, relatively little is known about subsequent long-term outcomes. Pain, anxiety and agitation are important stress factors for many critically ill patients. There are very few studies concerned with pain, anxiety and agitation and the consequences in older critically ill patients. The overall aim of this study is to identify how an ICU stay influences an older person's experiences later in life. More specific, this study has the following objectives: (1) to explore the relationship between pain, anxiety and agitation during ICU stays and experiences of the same symptoms in later life; and (2) to explore the associations between pain, anxiety and agitation experienced during ICU stays and their effect on subsequent health-related quality of life, use of the health care system (readmissions, doctor visits, rehabilitation, medication use), living situation, and survival after discharge and at 6 and 12 months of follow-up.

**Methods/Design:**

A prospective, longitudinal study will be used for this study. A total of 150 older critically ill patients in the ICU will participate (ICU group). Pain, anxiety, agitation, morbidity, mortality, use of the health care system, and health-related quality of life will be measured at 3 intervals after a baseline assessment. Baseline measurements will be taken 48 hours after ICU admission and one week thereafter. Follow-up measurements will take place 6 months and 12 months after discharge from the ICU. To be able to interpret trends in scores on outcome variables in the ICU group, a comparison group of 150 participants, matched by age and gender, recruited from the Swiss population, will be interviewed at the same intervals as the ICU group.

**Discussion:**

Little research has focused on long term consequences after ICU admission in older critically ill patients. The present study is specifically focussing on long term consequences of stress factors experienced during ICU admission.

**Trial Registration:**

ISRCTN52754370

## Background

Modern methods in intensive care medicine often enable the survival of older critically ill patients. The short-term outcomes for patients treated in intensive care units (ICUs), such as survival to hospital discharge, are well documented. However, relatively little is known about subsequent long-term outcomes [1]. It is generally recognized that survival alone is not the only important outcome following an ICU stay. Various stress factors experienced in the ICU and the severity of illness or injury have long-term consequences [2-4]. Over the long term, discomfort experienced in the ICU and stressful memories of an ICU stay have been associated with the development of acute posttraumatic stress disorder-related syndromes, anxiety, depression, and impaired health-related quality of life (HR-QOL) [5-9]. For some patients these symptoms are chronic and cause lasting personality changes. Other studies focus on outcomes such as functional status, ability to live at home, influence on the social network, and the burden on the family, all of which can, at times, be more important than the length of survival [10-12]. Recent research has indicated that there may be significant cognitive and emotional dysfunction following critical illness [13-15]. Another study shows that survivors of critical illnesses have increased health care system needs. Continuing hospital care, and/or rehabilitation, community support services or other healthcare services after the ICU stay were needed. In addition, there was an increase in the use of medication and of doctor visits [16]. An increasing proportion of critically ill patients are aged (65 years and older). Older patients with severe injuries are at risk of poor outcome [17]. Mortality rates are almost 22% in older surgical patients [18], and yet age alone does not appear to be a reliable predictor of outcome after ICU admission [19,20]. Older patients express preferences for longer life under compromised health conditions more frequently than healthy persons [21]. Until now, few studies have examined long-term outcomes after ICU admissions in older critically ill patients [17,22,23]. Pain, anxiety and agitation are important stress factors for many critically ill patients, yet these symptoms are difficult to distinguish from one another. Pain, anxiety and agitation can have consequences for the health-related quality of life [5]. In addition, pain, anxiety, and agitation, and their consequences for long-term outcomes, have rarely been examined in older critically ill patients in the ICU [24-26]. In contrast to other studies [22,23], the present study examines the relationship between the ICU stay and post-hospital pain, anxiety and agitation in older critically ill patients, and addresses whether acute experiences in the ICU can cause more serious chronic conditions after discharge. This article describes a longitudinal study in which older critically ill patients are followed one year after their discharge from the hospital. Under investigation were their pain experiences, levels of anxiety and agitation, health-related quality of life, and use of the health care system, in order to detect relationships between these main outcomes and their ICU experiences.

### Study Aims

The overall aim of this study is to identify how an ICU stay influences an older person's experiences later in life. The study addresses the following research questions: (1) Does an ICU stay influence the pain, anxiety, and agitation experienced by older critically ill patients after discharge, and at 6- and 12-month follow-up? (2) Do the pain, anxiety and agitation experienced by older critically ill patients during an ICU stay affect their experiences of these symptoms after discharge, and at 6- and 12-month follow-up? (3) Does an ICU stay affect the health-related quality of life (HR-QOL) of older critically ill patients after discharge, and at 6-and 12-month follow-up? (4) What is the relation between the ICU stay and subsequent use of the health care system (readmissions, general practitioner visits, rehabilitation, length of hospital stay), medication use, living situation, and survival as experienced by older critically ill patients after discharge, and at 6- and 12-month follow-up?

## Methods/Design

### Design

A prospective longitudinal study will be conducted in older critically ill patients admitted to the ICU. Data will be collected over a period of two years at the following intervals: during ICU admission and 1 week, 6 months and 12 months after hospital discharge. A flow chart of the study is presented in Figure 1.

**Figure 1 F1:**
[figure not shown]
**Flow Chart of the Study Design**. Schedule of the Study and Measurements of the ICU and Comparison Groups.

### Participants and Setting

The study will be conducted in the interdisciplinary ICU of a Swiss university hospital, where approximately 4000 patients with surgical procedures, illnesses, and trauma are treated each year, as well as at 12 follow-up clinics. From this ICU, 150 older critically ill patients (age 65 years and older) will be recruited, to be followed until 1 year after discharge from the hospital (the ICU group). A sample of 100 patients will be needed, based on a power analysis; with a 95% confidence interval for an estimated prevalence of pain between 0.30-0.50 and a total of 0.20, a sample size of 81-96 is needed. In order to ensure a large enough sample, and to counteract the potential loss of participants through mortality, relocation, attrition, or other problems, an additional 50 participants will be recruited (150 total). In order to be able to interpret trends in scores in the ICU group for the outcome variables *pain, anxiety*, *agitation, HRQOL*, *use of the health care system *(readmissions, GP visits, rehabilitation, length of hospital stay), *medication use, living situation*, and *survival*, we decided to collect similar data in a comparison group. Participants of the comparison group are a convenience sample of older people from the Swiss population, who have not been admitted to an ICU for the last 15 years. Through matching of age and gender, an attempt is made to increase the comparability of the groups at baseline.

### Inclusion and exclusion criteria

To participate in this study, the participants must have a minimum age of 65 years, have had an ICU stay of at least 48 hours (ICU group) or no stay for the last 15 years (comparison group), be able to speak and read either German or French, and live in Switzerland. Excluded were participants because of temporary tracheostomies, chronic mechanical ventilation, illness-related cognitive impairment (dementia), or psychotic illnesses including delusions and changes in mental state, and potentially terminal illnesses such as lung or heart diseases and cancer.

## Measurements

### Background data

Demographic data include age, gender and marital status. Furthermore, health-related data including Activities of Daily Living (ADL) and co-morbidities will be collected at baseline for all participants. The severity of the patient's condition will be determined using the Acute Physiology and Chronic Health Evaluation (APACHE II) and the Simplified Acute Physiology Score (SAPS II) [27]. The performance of ADL will be measured using items querying the need for assistance with daily activities (home health care, home food delivery, residence in a retirement home or nursing home) and various quality-of-life dimensions such as physical function, physical role function, vitality and social role function (Short Form 36 Health Survey [SF-36]). A scale developed for this study will be used to assess the need for assistance with daily activities (completely dependent; needs support by caregivers and special medical equipment; needs caregivers; independent with medical equipment; completely independent). Co-morbidities will be measured using the International Classification of Diseases (ICD), Version 10 [28].

### Pain, anxiety and agitation during an ICU stay

During the ICU stay, pain, anxiety and agitation will be measured in the ICU group. In patients unable to express pain themselves verbally, pain intensity will be measured using a behavioural pain scale employing three behavioural parameters--mimic, body movement, and muscle tone. The intensity of the behavioural parameters will be assessed on the basis of a four-point Likert scale: each characteristic will be rated as weak or absent, moderately severe, severe, or very severe. The validity of the scale has been determined to be adequate, and its interrater reliability is high (kappa value 0.80) ([name]. et al. Assessment of pain in sedated and mechanically ventilated patients: an observational study, submitted). Furthermore, potentially painful procedures will be recorded. The painful procedures include: intratracheal suctioning, dressing changes, repositioning in bed, and insertion of a central venous catheter [29]. Anxiety will be assessed using a numeric rating scale (0-10) (0 = no anxiety to 10 = worst possible anxiety) [30]. Agitation during the ICU stay will be measured using the German version of the Richmond Agitation-Sedation Scale (RASS), which has 10 levels, ranging from -5: unarousable (no response) to +4: combative (danger to staff). This scale has proven reliable for the assessment of critically ill patients in the ICU, with strong interrater reliability and criterion, construct, and face validity [31,32]. The Confusion Assessment Method for the ICU (CAM-ICU) will be used to assess delirium in the ICU [33], as well as general cognitive abilities, focusing on the following factors: a) acute onset or fluctuating course, b) inattention, c) disorganized thinking, and d) altered level of consciousness. This scale has been proven reliable and valid, with an interrater reliability kappa value of 0.96. Its sensitivity was 100% and 93%, with 98% and 100% specificity [34].

### Outcome indicators after discharge

In line with the study aims, the following outcome indicators will be measured in both the ICU group and the comparison group: (1) pain, anxiety and agitation, (2) HRQOL and (3) use of the health care system (readmissions, general practitioner visits, rehabilitation, length of hospital stay), medication use, living situation and survival. Pain intensity will be measured with a numeric scale (NRS) (0 = no pain to 10 = worst possible pain) [29,30], and pain frequency with a Likert-type scale (never, seldom, occasionally, often, always). Anxiety will be assessed using a numeric rating scale (0-10) and the Hospital Anxiety and Depression Scale (HADS-D), which uses two subscales--an anxiety scale (HADS-A) and a depression scale (HADS-D). Internal consistency (Cronbach's alpha) is 0.80 for HADS-A and 0.81 for HADS-D. The test-retest reliability shows the correlations r = 0.81 for HADS-A and r = 0.89 for HADS-D [35]. Agitation will be measured using the Confusion Assessment Method (CAM). The German or French Short Form of the Confusion Assessment Method (CAM) [36], including a telephone version for the 6- and 12-month follow-ups [37], will be used for all participants. The inter-observer reliability of the CAM is high (kappa = 0.81-1.0) [38]. Health-related quality of life (HR-QOL) will be assessed using the component scores of the Short Form 36 Health Survey (SF-36). As a comprehensive, generic, 36-item instrument, the SF-36 concentrates on the subjective evaluation of health: 1) physical function, 2) physical role function, 3) bodily pain, 4) general health perceptions, 5) vitality, 6) social role function, 7) emotional role function, and 8) mental health. The items vary from yes/no questions to those offering 6 levels of choice. All subscales have been adapted to yield assessment values between 0 and 100. The health care system assessment will include the number, cause, and length of hospital admissions and stays using APACHE-Diagnosis non-operative and operative diagnoses (1) cardiovascular, 2) respiratory, 3) gastrointestinal, 4) neurological, 5) sepsis, 6) trauma, 7) metabolic, 8) haematological, 9) other, 10) cardiologic surgery, 11) respiratory surgery, etc., the number and the length of rehabilitation periods (location, length, ambulatory, stationary, discharge location) and the number of GP visits. Medication therapy, and mortality incidence, will be collected from all subjects in the ICU and comparison groups over the course of the study. Medication therapy includes all sedative, analgesic, antipsychotic, psychotropic, steroidal, and vasoactive medications. The cumulative amount of medication will be recorded. Mortality incidence will be determined based on survival rates. For all instruments, French and German versions will be available. Translation of the SF-36 into German and French was done according to the Translation Protocols of the International Quality of Life Assessment Group [39,40]. The SF-36 Health Survey and the HADS-D have been used in a range of intensive care-related studies [5,41,42]. An overview of all measurements is summarized in Tables 1 and 2.

**Table 1 T1:** Measurements during ICU stay

Variables	Instruments	Sources
Pain (intensity, frequency)	Behavioural scale	PDMS/Q

Agitation (intensity, frequency)	RASS, CAM-ICU	PDMS/Q

Reasons for ICU admission (cause)	APACHE: diagnosis at admission	MR/Q

Severity of illness	APACHE II, SAPS II	PDMS

Note: RASS = Richmond Agitation-Sedation Scale. CAM-ICU = Confusion Assessment Method for the ICU. APACHE = Acute Physiology and Chronic Health Evaluation. SAPS = Simplified Acute Physiology Score. PDMS = Patient Data Management System. MR = Medical record. Q = Questionnaire.

**Table 2 T2:** Measurements in the ICU group and the comparison group (Follow-up)

Variables	Instruments	Time of Measurement		
		**Baseline/1 week after discharge ICU**	**6 months**	**12 months**

Pain (intensity, frequency)	NRS	Q	Q	Q

Anxiety (intensity, frequency)	NRS, HADS-D	Q	Q	Q

Agitation (intensity, frequency)	CAM	Q	Q	Q

Mortality	Survival: Yes/No	Q	Q	Q

Morbidity	International classification of diseases, version 10	MR/Q	MR/Q	MR/Q

Quality of life (HR-QOL)^1^	SF-36	Q	Q	Q

Note: NRS = Numeric rating scale. HADS-D = Hospital Anxiety and Depression Scale. CAM = Confusion Assessment Method. SF-36 = Short Form 36 Health Survey. HR-QOL = Health-related quality of life. MR = Medical record. Q = Questionnaire.

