### Procedure

Background data will be gathered via medical records and questionnaires. Medical and nursing staff will gather daily routine data regarding pain, anxiety, and agitation, along with any other information relevant to usual care in the ICU. Collection of data concerning pain, anxiety and agitation will be carried out by the staff who regularly care for the patients. For this study these caregivers have received special training. Data about the outcome indicators will be collected using questionnaires 1 week, 6 months and 12 months after discharge. It should be emphasized that participants in the ICU group will be asked one week after discharge to make an assessment of both their current HR-QOL and their HR-QOL, pain, anxiety and agitation intensity, before admission to the ICU. One week after ICU discharge, patients in the ICU group will be contacted and interviewed. The interviews will be carried out only if the patients are physically and psychologically fit to be interviewed. If necessary, help will be provided in filling out the questionnaire. All data will be collected using face-to-face (baseline) and telephone (follow-up) interviews and will be collected by 4 trained interviewers. The baseline interviews with all critically ill patients will take place in the hospital. All other interviews for both groups will take place by telephone. The SF36 and HADS-D will be mailed to all participants. In order for them to prepare themselves for the interview, both groups will be informed of the general nature of the questions ahead of time. Because unanswered questions would affect the evaluation of the questionnaires, an interviewer will check to ensure that all questions have been answered, and follow up in cases where information is lacking. If questionnaires are not returned, reminders will be sent to the participants.

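### After discharge, agitation is measured only with a tool whose ICU version the protocol describes as a delirium assessment, and no agitation intensity or frequency scale is named

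*Protocol article*

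**What the plan says.** **After discharge.** Under Outcome indicators after discharge, the protocol article states "Agitation will be measured using the Confusion Assessment Method (CAM"). The version that every participant receives is given as "The German or French Short Form of the Confusion Assessment Method (CAM) [36], including a telephone version for the 6- and 12-month follow-ups [37"]. No other agitation measure is named. Table 2 carries the row "Agitation (intensity, frequency) CAM", to be collected by questionnaire at 1 week, 6 months and 12 months in both groups.

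**In the ICU.** Under Pain, anxiety and agitation during an ICU stay, agitation is assigned to the Richmond Agitation-Sedation Scale (RASS), which has 10 levels from -5 (unarousable) to +4 (combative). The ICU version of the CAM is introduced separately: "The Confusion Assessment Method for the ICU (CAM-ICU) will be used to assess delirium in the ICU [33], as well as general cognitive abilities". Its four factors are onset or course, attention, organisation of thought and level of consciousness. Table 1, however, sets both RASS and CAM-ICU against agitation intensity and frequency.

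**Before the ICU.** Under Procedure, ICU patients are asked one week after discharge to recall their "HR-QOL, pain, anxiety and agitation intensity, before admission to the ICU". No scale is named for the agitation part.

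**What the data are for.** Under Study Aims, question 1 asks whether an ICU stay influences later pain, anxiety and agitation. Question 2 asks whether these symptoms in the ICU affect the same symptoms later.

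**The concern.** Agitation is one of the three symptoms on which the study is built. If the only post-discharge instrument for it is an assessment of confusion or delirium, two things follow. For question 1, the ICU and comparison groups would be compared on confusion while the result is reported as agitation. For question 2, a bedside agitation-sedation score would be related to a later confusion assessment, although the question concerns one symptom followed over time. A finding in either direction could then be misread: a difference as lasting agitation, or no difference as its absence.

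The article also promises two attributes, intensity and frequency, which the tool as described does not supply. If they are not collected at the three interviews, no later analysis can recover them.

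**Working it through.** No arithmetic decides this point, so the statements are set side by side.

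**Step 1. Instruments and promised attributes after discharge**

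| Symptom | Attributes in Table 2 | 0-10 intensity scale | Frequency scale in the text | Other instrument |
|---|---|---|---|---|
| Pain | intensity, frequency | yes (NRS) | yes (five categories, never to always) | none |
| Anxiety | intensity, frequency | yes (NRS) | none named | HADS |
| Agitation | intensity, frequency | none | none named | CAM only |

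Anxiety lacks a named frequency scale too, but it has a graded intensity scale. Agitation is the only one of the three with neither.

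**Step 2. What the tool is said to measure.** The only description of content is for the ICU version: delirium and general cognitive abilities, through four factors. The nearest to agitation is an altered level of consciousness, but nothing says that this is graded for agitation or counted over time. The performance figures quoted are sensitivity, specificity and kappa for the CAM-ICU, and kappa for the CAM. These describe agreement on a classification, not an intensity or frequency score.

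**Step 3. Consistency within the article.** The ICU text separates agitation (RASS) from delirium (CAM-ICU). Table 1 merges them under agitation. The post-discharge text and Table 2 keep only the CAM and call it agitation. These three placements do not agree on what the tool measures.

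**Step 4. What questions 1 and 2 would receive**

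- Question 1, agitation part: CAM in the ICU group against CAM in the comparison group, which is a comparison of confusion or delirium.
- Question 2, agitation part: RASS in the ICU against CAM later, which links two constructs. Pairing CAM-ICU with the later CAM would be more consistent, but it would be a question about delirium.
- Pre-ICU level: a recalled intensity with no named scale and no post-discharge intensity score to set it against.

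**Step 5. Is the sample size involved?** No. The article's one calculation is for pain prevalence. Taking its total of 0.20 as the full width of a 95% interval (half-width 0.10), n = 1.96² × p(1 − p) / 0.10². For p = 0.30, 3.8416 × 0.21 / 0.01 = 80.67, or 81. For p = 0.50, 3.8416 × 0.25 / 0.01 = 96.04. This reproduces the stated 81-96, and the agitation problem does not touch it.

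**The case against.** The strongest reply is that the article assigns delirium to the CAM-ICU, not to the short form and telephone version used after discharge. The items of those versions are not listed, so a shared construct is an inference from the common name and the ICU description. Table 1 also places the CAM-ICU under agitation, so one could pair like with like across the two phases. And a condensed article may leave item wording, including the pre-ICU recall item, to the full protocol.

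Much of this stands as a limit on the claim. It is an inference that the post-discharge CAM measures confusion, and the unnamed recall scale is only supporting evidence. But the reply does not supply an agitation measure. Table 1 repeats the conflation and contradicts the ICU text, and a CAM-ICU to CAM pairing would still concern delirium. Nor is this something merely left out: the article positively assigns the outcome to the CAM and states the attributes expected from it.

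A reader might infer more, and the document does not support it:

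- *CAM positives will be too few to analyse.* No CAM prevalence is given at any time point, so no event count or power can be derived. The 1-week assessment also falls soon after the ICU stay.
- *Averaging RASS would cancel agitation against sedation.* Data Analysis does not say that raw RASS scores will be averaged, and the choice of summary is commonly left to the analysis plan.
- *The exclusions remove the people whom the CAM would flag.* The wording "psychotic illnesses including delusions and changes in mental state" most naturally qualifies the psychotic illnesses. An entry criterion also cannot remove someone who becomes confused during follow-up.

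**Conclusion.** The point holds as a mismatch between outcome and instrument, and as an inconsistency about what the CAM measures. Its size is one of three core symptoms, in two of four research questions, at all three post-discharge assessments in both groups, with the pre-ICU recall also affected in the ICU group. The pain and anxiety parts of questions 1 and 2, questions 3 and 4, and the sample size are unaffected.

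It would go too far to say that the agitation parts of questions 1 and 2 cannot be answered. What the document supports is that the instrument as described does not answer them: the results would concern confusion or delirium unless an agitation measure is added or the outcome is renamed. The conclusion rests on one assumption, that the post-discharge CAM has broadly the content described for its ICU version. If the short form does yield a graded agitation score, the article needs to say so. No numerical effect on power or bias can be given from the document.

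**What to change.** 1. Report the CAM and CAM-ICU as measures of delirium/confusion in Outcome indicators after discharge and in Tables 1 and 2. RASS remains the ICU agitation measure.
2. Add a self-rated 0-10 item for agitation or restlessness, with the never-to-always categories already used for pain frequency, at 1 week, 6 months and 12 months in both groups. Use the same rating for the recalled pre-ICU agitation intensity and name it under Procedure.
3. If no item is added, reword the agitation parts of questions 1 and 2 and the agitation row of Table 2 as delirium/confusion, and state that later agitation is not measured.

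The cost of the first two steps is two short interview items and some relabelling. The items would have no validation of their own, and a self-rating is not on the same scale as the staff-rated RASS. Question 2 would then relate two measures of agitation, but not one instrument repeated over time, and the report should say so. The third step costs only wording, but gives up agitation as a follow-up outcome.
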